### 2.1. Design

This is a comparative cross-sectional study involving women post-GDM, named the Malaysian Nutritype (MyNutritype) study. The primary outcome is the nutritype signatures associated with T2D in Malaysian women post-GDM. The secondary outcomes of the study include the comparisons of anthropometric and clinical measurements, biochemical profile, energy and nutrient intake, and lifestyle practices between the three groups of women post-GDM (NGT, prediabetes, and T2D).

The aims of this study are:(a)To determine dietary patterns associated with T2D and prediabetes;(b)To determine the metabolomic profile associated with T2D and prediabetes using one-dimensional proton nuclear magnetic resonance (^1^H NMR) spectroscopy;(c)To identify nutritype signatures (association between dietary patterns and metabolomic profile);(d)To determine the nutritype signatures associated with T2D in women post-GDM;(e)To compare other parameters in women post-GDM with normal glucose tolerance (NGT), pre-diabetes and T2D, which include:i.Anthropometric and clinical measurements;ii.Biochemical profile;iii.Energy and nutrient intake;iv.Lifestyle practices.

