Multivariate data analysis of the processed spectra will be performed using SIMCA-P+ version 15.0 (Sartorius Stedim, Umeå, Sweden) by applying various statistical algorithms including principal component analysis (PCA), partial least square discriminant analysis (PLS-DA), and orthogonal projections to latent structures discriminant analysis (OPLS-DA) to determine differences in metabolites between the three groups. Based on the multivariate data analysis results, parts of the spectra (ppm) responsible for the differences between groups will be quantified using Chenomx software by matching the corresponding peak with the metabolite database. PCA score and loading plots will be drawn in SIMCA-P+ software to validate the data obtained from Chenomx software. Pathway identification will be based on the Kyoto Encyclopedia of Genes and Genomes (KEGG) (Kanehisa Laboratories, Kyoto, Japan).

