#### 2.5.9. Nutritype Signatures

Nutritype signature models will be developed based on the three-step chemometric strategy for nutrimetabonomics [42,43]. In step 1, dietary patterns, as assessed by PCA, will be used to identify the factor scores as described in Section 2.5.3. The factor scores will then be designated as “loadings (VFFQ)”. In step 2, factor scores will be coded to create dummy variables (UFFQ). Positive scores will be coded as class number one, whereas negative scores will be coded as class number two. In step 3, the coded factor scores of each dietary pattern will be regressed against the ^1^H NMR metabolite profile to identify the metabolic phenotypes (“loadings, VNMR”) associated with these dietary patterns using PLS-DA to maximise the separation between T2D and non-T2D groups. The corresponding loading plots from the PLS-DA analyses will determine the significant metabolites we will use to develop nutritype signature models [25]. Chemometric analysis will be performed to produce nutritype signature models using SIMCA-P 15.0+ software (Sartorius Stedim, Umeå, Sweden).

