### 2.7. Statistical Analysis

Statistical analysis will be performed using SPSS statistical software version 25.0 (IBM, Chicago, IL, USA). Data for categorical variables will be reported as number and percentage, while continuous data will be reported as mean ± standard deviation (SD). Data normality will be assessed prior to data analysis. The study will analyse the differences in the demographic characteristics between subjects who agreed to participate in the study versus those who did not agree to participate. Pearson’s correlation coefficient test will be used to determine correlations between continuous variables, the Chi-squared test to determine the association between categorical variables, and one-way analysis of variance (ANOVA) to compare the differences between the three groups. Multivariate linear regressions will determine the association between the metabolomic profile and factor scores of each dietary pattern yielded from PCA. Multinomial logistic regression will determine the factors, and the nutritype signature models associated with T2D. Variables significant at the bivariate level will be entered into the regression model as confounders. Crude and adjusted odds ratios (ORs) with a 95% confidence interval (CI) will be presented. Subgroup analyses will also be performed, such as early versus late postpartum (<1 year versus ≥1 year post-GDM), supplement versus nonsupplement users, and obese versus nonobese subjects. A previous study found different risk factors of T2D at early (<1 year) versus late postpartum (≥1 year) following GDM [4]. In case of missing data, the study will report the number of available data for the variable. We will analyse any differences in the characteristics between reporters versus nonreporters. A *p*-value < 0.05 for all statistical tests will be considered significant.

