Our study aims to determine the associations between metabolomic profile and dietary patterns, and subsequently develop nutritype signature models. We will then determine which combination of dietary pattern and metabolomic profile is directly and significantly associated with T2D in women post-GDM. The findings on nutritype signatures will support the development of early prevention measures against T2D in women post-GDM. Metabolomics is commonly applied in nutrition research to assess responses to specific dietary patterns, discover biomarkers related to diet and disease, and subsequently determine the most effective dietary interventions to prevent diseases [50,51]. The field of nutritional metabolomics, which integrates metabolomics with nutrition in complex biosystems, may provide insight into the mechanisms linking diet and disease [48].

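### Step 3 of section 2.5.9 gives one PLS-DA two incompatible targets, diet class and T2D status; if T2D guides the fit or the metabolite choice, the primary test is circular.

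*Protocol article*

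**What the plan says.** **Building the signature (section 2.5.9).** Step 1 takes factor scores from the dietary PCA. Step 2 codes each score as one of two classes, positive or negative. In step 3 "the coded factor scores of each dietary pattern will be regressed against" the NMR metabolite profile, to find metabolic phenotypes linked to the dietary patterns. The same sentence ends by saying this is done "using PLS-DA to maximise the separation between T2D and non-T2D groups". The loading plots of this PLS-DA "will determine the significant metabolites we will use to develop nutritype signature models".

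**Testing the signature (section 2.7).** "Multinomial logistic regression will determine the factors, and the nutritype signature models associated with T2D", with crude and adjusted odds ratios and 95% confidence intervals. A p-value "< 0.05 for all statistical tests will be considered significant".

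**Standing of the test.** Section 2.1 states: "The primary outcome is the nutritype signatures associated with T2D in Malaysian women post-GDM". The Discussion says the study will "determine which combination of dietary pattern and metabolomic profile is directly and significantly associated with T2D".

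**Sample and data.** The study is cross-sectional with at least 126 women (section 2.3). Spectra are divided into 1000 bins (section 2.5.8). Section 2.5.8 also says that the parts of the spectra "responsible for the differences between groups will be quantified using Chenomx software", the groups being NGT, prediabetes and T2D.

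**The concern.** PLS-DA finds directions in the metabolite data that covary most with a class label supplied to it. Step 2 defines that label as high or low dietary score. The end of step 3 implies that the label is T2D status. An analyst cannot follow both instructions with one model, and the choice decides what the signature is.

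If the label is diet class, the signature describes diet, and its association with T2D is an open question that the regression in section 2.7 can answer. If T2D status steers the fit or the choice of metabolites, the signature is built to differ between T2D and non-T2D. Testing it for that difference in the same women then gives the data's answer back to the data. The odds ratios, confidence intervals and p-values of the primary analysis would have no valid interpretation, and the signature would no longer be a description of diet alone.

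**Working it through.** **1. The plan's own figure.** The plan gives no number for this point. Its sample size is an input and can be partly rebuilt: 99 / 3 = 33 per group; 33 / (1 − 0.20) = 41.25, rounded up to 42; 42 × 3 = 126, as stated. The 99 itself cannot be rebuilt, because no mean difference or SD is given.

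**2. Why a T2D-tuned score must look associated.** Let X be the centred and scaled metabolite matrix (n women, p variables) and y the centred T2D indicator.
- First PLS weight: w = X′y / ‖X′y‖. Score: t = Xw.
- Then y′t = y′XX′y / ‖X′y‖ = ‖X′y‖, which is positive in any sample, whether or not an association exists.
- With independent variables and no true association, corr(t, y)² is about p / (p + n).
- p = 1000, n = 126: 1000 / 1126 = 0.888, so r is about 0.94.
- p = 40, n = 126: 40 / 166 = 0.241, so r is about 0.49.
- With n = 126, |r| of about 0.175 is enough for two-sided p < 0.05.

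The formula does not involve the number of T2D cases. It also shows that the problem does not need 1000 bins: 40 quantified metabolites are enough.

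**3. Simulation under the null (no link between metabolites, diet and T2D).** Settings: N = 126 with 42 or 15 T2D cases, and N = 99 with 33; 1000 bins (independent, or driven by 30 or 10 latent factors) or 40 independent metabolites; 600 to 1000 runs per setting. The score was tested against T2D by a logistic likelihood-ratio test at two-sided 0.05.

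| How the signature is built | Null rejection rate |
|---|---|
| PLS-DA on T2D, 1 or 2 components, same women | 100% in every setting |
| Sum of the 10 variables most related to T2D, same women | 100% in every setting |
| PLS-DA on diet class only, same women | 4.0% to 7.1% |
| PLS-DA on T2D in one half, tested in the other half | 4.8% to 6.8% |
| Metabolites preselected on T2D, then PLS-DA on diet class | 60% to 73% (1000 bins); about 30% (40 metabolites) |

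The Monte Carlo standard error at 5% is √(0.05 × 0.95 / 600) = 0.9 points for 600 runs and 0.7 points for 1000. The 7.1% is the highest of 24 diet-only estimates (12 settings × 2 component numbers), and any real excess there is negligible beside 100%.

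**4. A second null simulation.** N = 126, 1000 correlated bins, 42 or 13 T2D cases, 300 runs each, t-test on the score. A two-component T2D-tuned score, and the sum of its top 15 bins, rejected in 100% of runs. A signature derived from diet alone rejected in 5.0% to 5.7%.

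**5. Side by side.** Two readings of one sentence lead to a type I error of about 5% or of 100% for the primary test.

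**The case against.** The best defence is that the operational steps concern diet throughout. Step 1 derives dietary scores, step 2 codes them, and step 3 regresses the coded scores and looks for phenotypes linked to dietary patterns. No step codes T2D as a response. Section 2.7 again relates metabolites to dietary factor scores and treats T2D in a separate regression. On this view the T2D clause is loose wording and the analysis is sound.

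Much of this stands. A reader might infer that the primary result will be significant even if no association exists. The article does not support that: it does not establish that T2D enters the fit, and on the diet reading the test holds about its nominal level. What the defence cannot do is remove the clause. It states the purpose of the very model whose loadings pick the signature metabolites.

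Two further points on the other side are fair. The three-step strategy comes from cited work that is not at hand, and a condensed article may leave internal validation to the full protocol. The point therefore does not rest on missing validation. Nor would validating the PLS-DA itself repair a later regression on scores or metabolites chosen in the same women. Also, a reader might infer from the group-based quantification in section 2.5.8 that T2D-driven selection occurs even on the diet reading. Section 2.5.9 does not say that those metabolites are the input to step 3, so the 30% to 73% rates show a risk to be ruled out and are not a finding about the plan.

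**Conclusion.** The contradiction is certain: one PLS-DA is given a dietary response and a T2D objective. Circularity is conditional on T2D actually guiding the fit or the metabolite selection, as the clause says. If it does, the primary odds ratios, intervals and p-values are invalid, with null rejection of 100% in all simulated settings. If diet class is the only response and no metabolite is chosen on T2D, the rate is about 4% to 7%. Because the sentence governs the primary outcome, it must be reconciled before analysis.

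The sizes rest on assumptions: T2D counts of 13, 15, 33 or 42 (the article gives none), the bin correlation, the number of components, 1000 bins or 40 metabolites as the input to step 3, a single score as the form of the signature, and an unadjusted two-group test in place of the multinomial model. The 100% did not change across any of the settings tried.

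**What to change.** In step 3 of section 2.5.9, delete the closing clause about maximising the separation between T2D and non-T2D. State that the dietary-pattern score or class is the only PLS response, and that T2D status is withheld from both model fitting and metabolite selection. State also that the metabolite profile entering step 3 is not limited to regions chosen in section 2.5.8 because they differ between the glycaemic groups. Then test the diet-derived signature against T2D as section 2.7 describes.

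If a T2D-tuned model is also wanted, report it separately and only from held-out scores, with the metabolite selection and the fit repeated inside each cross-validation fold, or inside each permutation of the T2D labels.

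The cost is a few sentences and a little computing. Apparent associations with T2D will be weaker than those from a T2D-tuned signature.

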#### 2.5.3. Dietary Patterns

The study dietitian will administer a semiquantitative food frequency questionnaire (FFQ) adapted from the nationwide Malaysian Adult Nutrition Survey, to determine food consumption in the past month [21]. It contains 14 food groups: grain and cereal products; fast food; meat and poultry; fish and seafood; eggs; legumes, seeds and nuts; milk and dairy products; vegetables; fruits; beverages; alcoholic drinks; confectionaries; bread spread; and condiments. The portion size of the food items will be according to the Food Portion Sizes of Malaysian Foods Album [22]. The amount consumed food will then be converted into grams per day for each food item [10].

Dietary patterns will be derived based on PCA. Data suitability for factor analysis will be assessed prior to performing PCA [23,24]. Food items will be classified based on similarities in nutrient profiles and previous local studies [24,25,26]. The factor scores will be orthogonally rotated by varimax transformation to increase loading differences for easier interpretability [24,27]. Eigenvalue cut-off > 1.5 will determine the number of factors [28]. Food items with factor loadings < ±0.3 will be removed from further analysis [24,28]. A high factor score, whether positive or negative, indicates a high intake of that food group in dietary pattern; and vice versa [23,27].

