#### 2.5.8. Metabolomic Profile

NMR sample preparation for plasma and urine will be performed according to published protocols [40,41]. About 2 mL of the fasting blood will be collected into lithium heparin tubes, centrifuged at 1500× *g* for 20 min, divided into aliquots, frozen in a liquid nitrogen tank, and stored at −80 °C until further analysis. Subjects will also have to collect mid-stream urine into a urine container. Sodium azide 0.1% will be added to the urine sample to prevent microbial growth. The urine samples will be centrifuged at 1500× *g* for 10 min, divided into aliquots, and stored at −80 °C until further analysis.

Upon thawing, 500 μL of plasma will be vortexed for 1 min, then centrifuged for 2 min at 5000× *g* to remove solid debris. We will transfer 400 μL of plasma supernatant into a 0.5 mL ultra-centrifugal filter and centrifuged at 6000× *g* for 30 min to remove macromolecules, including lipids and proteins. We will mix 200 μL of plasma filtrates with 400 μL of phosphate buffer solution (potassium dihydrogen phosphate Kh_2_Po_4_]) prepared in deuterium oxide (D_2_O) containing 0.1% trimethylsilyl propanoic acid (TSP) and 0.1% imidazole). A total of 600 μL of prepared samples will be transferred to 5 mm NMR tubes. For urine, 400 μL of thawed sample will be added to 200 μL of phosphate buffer solution, then centrifuged at 4800× *g* for 5 min before being transferred to NMR tubes.

The nontargeted metabolomic analysis will be performed using a ^1^H-NMR platform. ^1^H-NMR spectra will be acquired using a 500 MHz NMR spectrometer (Varian Inc., Palo Alto, CA, USA). Spectral data will be preprocessed using Chenomx NMR suite software version 9.0 (Chenomx Inc., Edmonton, AB, Canada) by Fourier transformation, auto-phasing, and auto-baseline correction. Spectral data will be divided into 1000 equal bins, digitised into a table of common integral, and exported as a text file for multivariate data analysis.

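### Metabolites are declared significant from PLS-DA loading plots and then tested at an unadjusted 0.05 in the same women, so neither rule controls false positives

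*Protocol article*

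**What the plan says.** The route from spectrum to signature runs through three sections of the protocol article.

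- **Section 2.5.8.** Plasma and urine are both analysed, without preselected targets. "Spectral data will be divided into 1000 equal bins", and the bins go into PCA, PLS-DA and OPLS-DA. The spectral regions that these models find to differ between the three glucose groups are then identified and quantified, and they lead on to pathway identification.
- **Section 2.5.9.** Women are coded by the sign of their score on each dietary pattern, and "the coded factor scores of each dietary pattern will be regressed against the ^1^H NMR metabolite profile" by PLS-DA. The stated purpose includes setting T2D apart from non-T2D as far as possible. Then: "The corresponding loading plots from the PLS-DA analyses will determine the significant metabolites we will use to develop nutritype signature models".
- **Section 2.7.** Linear regressions relate the metabolomic profile to each pattern's scores, ANOVA compares the three groups, and multinomial logistic regression relates the signature models to T2D. "A *p*-value < 0.05 for all statistical tests will be considered significant".

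The number of patterns is not fixed in advance: "Eigenvalue cut-off > 1.5 will determine the number of factors" (Section 2.5.3). Section 2.1 makes the nutritype signatures associated with T2D the primary outcome.

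**The concern.** A loading plot ranks features by their weight in a fitted model. Some features always rank highest, whether or not any signal exists, so the plot carries no error rate and cannot by itself show that a metabolite is significant. With about 1000 bins and 126 women, a PLS-DA model can also separate randomly labelled classes.

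The p-value rule does not repair this. Features chosen because they track a dietary pattern are regressed on that pattern's score. Features chosen because they differ between glucose groups are compared between those groups. In both cases the same women supply the selection and the test, so a p-value below 0.05 is close to guaranteed by the selection.

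The selected metabolites feed the signature models, the pathway work and the T2D regression. Any error therefore reaches the primary outcome.

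**Working it through.** **1. Inputs.**
- Sample size: 126 (Section 2.3). It reproduces as 33 per group inflated for 20% loss: 33 / (1 − 0.20) = 41.25, rounded up to 42, and 3 × 42 = 126.
- Bins per spectrum: 1000. Fluids: 2 (Section 2.5.8).
- Dietary patterns: not fixed; 3 to 5 is assumed here. The search space is then 1000 × 2 × 3 = 6000 to 1000 × 2 × 5 = 10,000 feature-pattern pairs.
- Significance level: 0.05, unadjusted (Section 2.7).

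**2. What the two rules do when nothing is associated.** Null simulation: 126 women, 1000 bins, a random class label, two-component PLS-DA, sevenfold cross-validation, 200 runs. Bins were independent, or in 60 or 30 blocks with correlation 0.7 within a block.

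| Mean over runs | Independent | 60 blocks | 30 blocks |
|---|---|---|---|
| Apparent R2Y | 0.987 | 0.733 | 0.571 |
| Apparent class accuracy | 100% | 94.8% | 87.3% |
| Cross-validated Q2 | −0.145 | −0.550 | −0.533 |
| Cross-validated accuracy | 48.3% | 48.7% | 49.7% |
| Bins with p < 0.05, of 1000 | 49.7 | 47.3 | 50.7 |
| Top 30 bins by first-component weight with p < 0.05 | 100% | 97.7% | 95.1% |

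The fitted model looks convincing, while cross-validation shows that it predicts nothing. The last row has a simple cause. With scaled bins and a two-class label, the first PLS weight of a bin is proportional to its correlation with the label, so ranking by weight is ranking by p-value. On average 1000 × 0.05 = 50 null bins fall below 0.05, and the top 30 come almost entirely from those.

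A second null simulation (42 T2D against 84 non-T2D, 1000 bins, 300 runs) built a score from the 30 selected bins. The score was associated with the label at p < 0.05 in every run.

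**3. What share of p < 0.05 findings would be false.** With a fraction π of features truly associated:

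share false = 0.05(1 − π) / [0.05(1 − π) + power × π]

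| π | 80% power | 50% power |
|---|---|---|
| 1% | 86% | 91% |
| 5% | 54% | 66% |
| 10% | 36% | 47% |
| 20% | 20% | 29% |

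The share is one half at π = 0.05 / (0.05 + power): 0.05 / 0.85 = 5.9% at 80% power and 0.05 / 0.55 = 9.1% at 50% power. The documents give no value for π.

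**4. Even a short list has no protection.** For m independent null metabolites the chance of at least one p < 0.05 is 1 − 0.95^m: 64% for m = 20, 92% for 50 and 99% for 100. These values of m are assumptions, since the number quantified is not stated.

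**5. Where an adjustment has to be applied.** In null runs, Benjamini-Hochberg at 5% applied only to the top-weighted bins passed about 91% to 100% of them, depending on the correlation and the number kept (20 or 30). Applied to all 1000 bins, it gave any false discovery in about 4% of runs. Adjustment after selection therefore does little; adjustment over the set before selection works.

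**The case against.** Several points on the other side stand.

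- **The bins are not tested one by one.** A reader might infer 50 false positives per fluid, or 300 over two fluids and three pairwise group contrasts. The documents do not support either count. Bins enter multivariate models, only selected regions are quantified, and Section 2.7 plans a three-group ANOVA rather than pairwise contrasts.
- **A majority of false findings is not shown.** That needs a low fraction of truly associated features, on which the documents are silent. Nor do they establish that the findings would fail to replicate.
- **The PCA step is not offered as validation of PLS-DA.** The sentence "PCA score and loading plots will be drawn in SIMCA-P+ software to validate the data obtained from Chenomx software" concerns the quantified metabolite data. It is a different check and is not at fault.
- **This is a journal article, and the study is exploratory.** Cross-validation and permutation settings may sit in a fuller plan or in the cited chemometric strategy, and their absence here is no finding. The discussion also limits the study to associations.

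The last point does not dispose of the matter, because the article does not merely stay silent. It states that loading plots settle significance and that 0.05 applies to all tests. A fuller plan that controlled the false discovery rate would contradict the second statement. The exploratory label also sits beside a primary outcome built from these metabolites.

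**Conclusion.** The two stated rules are wrong as written and should be changed before analysis. Under the null, 95% to 100% of the 30 top-ranked bins pass p < 0.05, and a score made from such bins was associated with the label in every run. When selection and test use the same contrast in the same women, the p-value confirms nothing.

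For the primary outcome, the problem is direct if T2D labels enter the construction of the signature. Section 2.5.9 points that way, and so does Section 2.5.8 if the signature uses only regions already chosen for differing between glucose groups. If the signature is built wholly without T2D labels, the final T2D test is not circular by this route, but the choice of metabolites within the signature remains uncontrolled.

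The size rests on simulated normal bins with a simple correlation structure, two PLS components and 30 retained features; real spectra will differ in detail. The conclusion does not extend to a claim that most reported metabolites will be false: at 80% power that holds only below about 6% truly associated features.

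**What to change.** 1. **Section 2.5.9.** Interpret a PLS-DA model only if its cross-validated Q2 exceeds that of at least 1000 label permutations. Use loadings only to describe a model that passes, not to declare metabolites significant.
2. **Section 2.7.** For metabolite-level tests, replace p < 0.05 with Benjamini-Hochberg control at 5% over the full set before selection: all bins, or all metabolites quantified without regard to group or pattern, times fluids times patterns. Do not adjust over the selected features alone.
3. **Primary test.** Keep nominal 0.05 for signature against T2D only if T2D labels play no part in building the signature, including the choice of regions to quantify. Otherwise repeat the whole selection and model-building inside each cross-validation fold or permutation.
4. **Section 2.5.8.** Keep the PCA check of the Chenomx data, but do not present it as validation of the supervised models.

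**Cost.** New wording, routine computing and possibly more metabolites to quantify; no extra visits or samples. Fewer metabolites will be declared significant. As an illustration, 33 per group with 80% power at two-sided 0.05 implies a difference of √[2 × (1.960 + 0.842)² / 33] = 0.69 SD. At the Bonferroni level for 50 metabolites (0.05 / 50 = 0.001), power for that difference is 31% with 33 per group and 45% with 42. Benjamini-Hochberg is less strict than this, but the single-comparison sample size should not be expected to carry full power at metabolite level.
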